## Methods/design

### Study design

This study is a prospective randomised controlled trial. It will be conducted from April 2014 to August 2015 at 14 hospitals around China^a^. Five hundred and sixty participants are planned to be recruited via advertisements in newspapers, television, websites and posters. After being diagnosed by physicians of the gastroenterology or anorectal departments, participants will receive a 2-week long assessment (the stool diary). Randomisation will be performed centrally by the Clinical Evaluation Centre of the China Academy of Chinese Medical Sciences in Beijing, and eligible participants will be randomised into the EA group or the control group. After the baseline assessment has been carried out and the informed consent has been obtained, a randomisation number will be sent to the acupuncturist by phone or online. The statisticians, outcome assessors, and physicians will be blinded to the allocation. The flowchart of the trial is presented in Figure 1. The duration of the trial is 34 weeks, including a 2-week long baseline assessment period (week-2-0), 8-week long treatment period (week 1–8), and 24-week long follow-up period (week 9–32). The time frame of the trial is presented in Figure 2. The trial protocol is in accordance with the principles of the Declaration of Helsinki and has been approved by the review board and ethics committee of the participating hospitals.

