#### Control group

Prucalopride Succinate (Janssen S.P.A) will be taken orally at a dose of 2 mg/day before breakfast for 8 weeks. Participants will undergo an electrocardiogram (ECG) at the 8^th^ week, and the drug will be taken for another 24 weeks in the absence of adverse events (like Q-T elongation).

The use of other medicine for constipation will not be allowed during the trial. Bisacodyl (5–10 mg) and Enemia Glycerini (110 ml) can be used for participants who fail to have a bowel movement for 3 or more consecutive days. Furthermore, the use of Bisacodyl and Enemia Glycerini should be recorded on the case report form.

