### Outcome measures

The outcome measures are based on the stool diary. The participants complete a stool diary, which is checked by outcome assessors and finally recorded in the Remote Data Capture (RDC) system. The contents of the stool diary include SBMs within 24 hours, straining degree, complete evacuation, stool consistency, use of drugs, etc. Participants will be asked to finish the diaries every day during the baseline assessment period, week 1–8, 11–12, 15–16, 19–20 and 31–32.

This trial includes one primary outcome measure and 8 secondary outcome measures. The primary outcome is the proportion of patients having ≥3 SCBMs/week, averaged over week 3–8. The secondary outcome measures are presented in Table 1. The safety of EA will be evaluated based on various events, including fainting, severe pain, haematoma, local infection, and any feeling of discomfort. The side effects of prucalopride include diarrhoea, nausea, abdominal pain, headache, palpitation, myocardial ischemia (presented in ECG), etc. Any adverse event resulting from EA or adverse drug reaction will be recorded.

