### Sample size and statistical analysis

The sample size will be based on the primary outcome (the proportion of patients having ≥3 SCBMs/week averaged over week 3–8). According to our pilot trial and the literature [4], the proportion of participant having ≥3 SCBMs averaged over week 3–8 was 31.6% for the EA group and 30.9% for the prucalopride group. The figure for the placebo group was 12.0% [4]. Thus, a non-inferiority margin of 10% is reasonable. To assess the non-inferiority between the treatment and control groups, a sample size of 276 for each group will be sufficient, with a one-sided 5% level of significance, a power of 80% and allowing for a 20% dropout. In this trial, we aim to recruit 560 participants, 40 for each hospital.

The data from the 14 centres will be pooled, and the Clinical Evaluation Centre of the China Academy of Chinese Medical Sciences in Beijing will conduct the statistical analysis using the SAS 9.1.3 (SAS Institute, Cary, NC, US) and SPSS Ver.13.0 (SPSS Inc., Chicago, IL, USA) software. The data analysis is based on the intention-to-treat (ITT) population. All statistical analyses will be two-sided tests except for the primary outcome. The level of significance will be established at 0.05. Continuous data will be represented by the mean, standard deviation, median, minimum value, and maximum value; categorical data will be represented by percentages. To compare two independent samples, a t-test or nonparametric test will be used for continuous data, and a chi-square test/the Fisher exact test/nonparametric tests will be used for categorical data. For the primary outcome, the CMH test will be used to avoid the centre effect. The analysis methods for secondary outcomes are presented in Table 1. For safety analysis, the incidence of adverse events will be compared between the two groups using the chi-square test or the Fisher exact test.

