## Discussion

Acupuncture has been used to treat constipation in China for thousands of years. Clinical practice and several trials showed that acupuncture is effective for constipation [13, 14]. However, the effect of acupuncture on severe constipation has not been evaluated. A protocol of EA versus sham acupuncture for severe constipation has been published [15].

This is a study design for a non-inferiority, randomised controlled trial aimed to compare the short-term effect (the 3^rd^ to 8^th^ treatment week) of EA with prucalopride for severe chronic constipation. Acupuncture is a non-toxic, economical intervention with minimal adverse effects [16]. If the efficacy of EA is non-inferior to prucalopride, it may be a reasonable option for patients who do not want to experience the side effects of prucalopride. We also want to observe EA’s lasting effect, i.e., EA’s effect at the 3^rd^ and 6^th^ month post treatment. The EA group will be treated for 8 weeks and the prucalopride group will be treated for 32 weeks. A comparison between the two groups after the 8^th^ week could clarify the lasting and dominant effect of EA.

This trial was limited because the participants and acupuncturists could not be blinded. However, the outcome assessors and statistician will be blinded to the allocation.

In conclusion, the trial will compare the effect of EA to that of prucalopride for severe chronic constipation.

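### Adverse-event incidence is compared crudely although electroacupuncture lasts 8 weeks and prucalopride up to 32, and recording is described by attribution, so the safety contrast is confounded with treatment duration

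*Protocol article*

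**What the plan says.** Five statements in the protocol article bear on the safety comparison.

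- **Test** (Sample size and statistical analysis): "the incidence of adverse events will be compared between the two groups using the chi-square test or the Fisher exact test". No counting window and no adjustment for time on treatment is given.
- **Recording** (Outcome measures): "Any adverse event resulting from EA or adverse drug reaction will be recorded". The examples differ by arm. For EA they are "fainting, severe pain, haematoma, local infection, and any feeling of discomfort". For prucalopride they are gastrointestinal complaints, headache, palpitation and ischaemia seen on ECG, with the list left open.
- **Duration** (Discussion): "The EA group will be treated for 8 weeks and the prucalopride group will be treated for 32 weeks". The Control group section makes the later part conditional: "the drug will be taken for another 24 weeks in the absence of adverse events (like Q-T elongation". So 32 weeks is a planned maximum.
- **Follow-up** (Study design): "8-week long treatment period (week 1–8), and 24-week long follow-up period (week 9–32". This applies to both arms.
- **ECG** (Control group): "Participants will undergo an electrocardiogram (ECG) at the" end of the first 8 weeks. No ECG is described for the EA arm.

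The Discussion relies on the safety contrast. If EA is non-inferior, "it may be a reasonable option for patients who do not want to experience the side effects of prucalopride". It mentions the 8 versus 32 weeks only in connection with efficacy after week 8.

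**The concern.** If an event counts when it is attributed to the patient's own treatment, the time in which a countable event can begin is about 8 weeks in the EA arm and up to 32 in the control arm. Few events in weeks 9–32 can be put down to needling that stopped at week 8, whereas a drug reaction can appear at any time while the drug is taken. A single crude proportion per arm then reflects length of treatment as well as tolerability. An ECG done in one arm only adds a way of finding events in that arm alone.

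What is at stake is the secondary message of the trial. A lower event proportion under EA could be read as better tolerability when part or all of it comes from shorter exposure. The primary efficacy outcome is not affected.

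**Working it through.** The article gives no adverse-event figure, so there is none to reproduce. The check asks how often the stated test would declare a difference if the two treatments had the same 8-week incidence and events were counted to week 32.

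**Inputs from the article**
- Treatment duration: 8 weeks versus up to 32, a ratio of at most 4.
- Test: two-sided at 0.05.
- Sample size: 560 patients. Assuming 1:1 allocation, 560/2 = 280 per arm, or 280 × 0.8 = 224 after the planned 20% dropout.

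**Assumptions, because the article gives no values**
- 8-week incidence p8 of 2%, 5%, 10% or 20%, equal in both arms.
- No countable EA events after week 8.
- Either a constant weekly hazard on drug, or a share f of 32-week drug events starting by week 8.

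**Formulas**
- Constant hazard: h = −ln(1 − p8)/8, so p32 = 1 − exp(−32h) = 1 − (1 − p8)^4. Example: 1 − 0.95^4 = 18.5%.
- Front-loaded onset: p32 = p8/f. Example: 5%/0.5 = 10%.
- Chance of declaring a difference: Φ[(d − 1.96·s0)/s1], with d = p32 − p8, s0 = √[2·p̄(1 − p̄)/n], p̄ the mean of the two proportions, and s1 = √{[p8(1 − p8) + p32(1 − p32)]/n}.

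**Worked cases, n = 280**
- 5% v 18.5%: d = 0.1355, s0 = 0.0272, s1 = 0.0266. (0.1355 − 1.96 × 0.0272)/0.0266 ≈ 3.08, giving 0.999.
- 5% v 10%: d = 0.05, s0 = 0.02226, s1 = 0.02216. (0.05 − 1.96 × 0.02226)/0.02216 ≈ 0.29, giving 0.61.

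| Onset of drug events | EA, 8 weeks | Prucalopride, 32 weeks | P(difference declared), n = 280 |
|---|---|---|---|
| Constant hazard | 2% | 7.8% | 0.89 |
| | 5% | 18.5% | 0.999 |
| | 10% | 34.4% | about 1 |
| | 20% | 59.0% | about 1 |
| 50% by week 8 | 5% | 10% | 0.61 |
| | 10% | 20% | 0.91 |
| | 20% | 40% | 0.999 |
| 75% by week 8 | 5% | 6.7% | 0.13 |
| | 10% | 13.3% | 0.23 |
| | 20% | 26.7% | 0.46 |
| 90% by week 8 | 5% | 5.6% | 0.05 |
| | 10% | 11.1% | 0.06 |
| | 20% | 22.2% | 0.09 |

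With 224 per arm and a constant hazard, the first two rows become 0.81 and 0.99.

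The formula counts only results pointing against prucalopride. The other tail matters only in the last rows, where it adds about one percentage point at most. At 5% v 5.6% it is Φ[(−0.0056 − 1.96 × 0.0189)/0.0189] = Φ(−2.25) ≈ 0.01.

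Two further results under a constant hazard:
- The crude incidence ratio is 2.9 to 3.9 against the drug at equal weekly hazards.
- If EA's weekly hazard were twice the drug's, EA would still show fewer events: 1 − 0.95² = 9.8% against 18.5%.

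Restricting the comparison to weeks 1–8 makes the two expected proportions equal in every row, and the test then keeps its nominal level.

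**The case against.** The case on the other side has real substance.

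- **No counting window is stated.** Weeks 1–8 are called the treatment period, and a test restricted to them would fit the text. Windows are often left to an analysis plan, which is not shown. This stands for the window alone. It does not cover the recording rule, which governs data collection: an analysis plan cannot recover events that were never written down.
- **The text does not say that other events go unrecorded.** Elsewhere it speaks of coding and comparing adverse events without restriction, and both example lists are open-ended. This stands: attribution-only recording is the natural reading of the rule, not its wording.
- **The direction is not certain.** A reader might infer that the comparison must be biased towards EA. The exposure and ECG components work that way, but the discomfort item sets a low threshold for EA. EA patients also attend 5 × 2 + 3 × 6 = 28 sessions in 8 weeks, which gives many occasions to report. The documents do not show the net balance.
- **Longer drug treatment is part of the regimen.** Calendar follow-up is equal, and a 32-week comparison of the two regimens with events recorded whatever their cause would be legitimate. The fault therefore lies in attribution-based recording combined with unequal treatment time, not in the chi-square test as such.
- **The ECG point is minor.** It is a single check before the drug is continued.

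**Conclusion.** The concern holds in a limited form. On the natural reading of the recording rule, a crude comparison over the whole trial gives the arms about 8 and up to 32 weeks in which a countable event can arise. It therefore confounds safety with treatment duration and tends to favour EA, with a possible partial offset from the discomfort item and the frequent EA visits.

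The size cannot be fixed from the article. It depends mainly on when drug reactions start. It is severe under a constant hazard, still large if half of drug events start by week 8, modest to moderate at 75%, and close to the nominal level at 90%.

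A reader might take the figures above 99% as the expected false-positive rate. That is not supported. They require a constant hazard over the full 32 weeks. Moreover, the test's own hypothesis is equal cumulative incidence, which is truly false in those scenarios; what misleads is reading the result as a difference in tolerability while on treatment.

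This should be corrected, but it does not threaten the primary analysis.

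**What to change.** 1. Record all adverse events in both arms on one common form at the same scheduled contacts, with attribution to treatment as a separate field.
2. Name weeks 1–8, when both arms are on treatment, as the between-group safety comparison. The chi-square or Fisher exact test can stay.
3. Report weeks 9–32 separately, either per patient-week of treatment or explicitly as an all-cause comparison of the two regimens.
4. Tabulate findings from the control-only ECG apart and keep them out of the between-group test.

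The cost is a revised form, a few sentences of analysis text and slightly more event recording. Treatment, schedule and sample size are unchanged. With 19 of 560 participants recruited at the time of the article (Trial status), almost all safety data can still be collected under the revised rule. Events already missed in those 19 may not be recoverable and should be noted.

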## Discussion

Acupuncture has been used to treat constipation in China for thousands of years. Clinical practice and several trials showed that acupuncture is effective for constipation [13, 14]. However, the effect of acupuncture on severe constipation has not been evaluated. A protocol of EA versus sham acupuncture for severe constipation has been published [15].

This is a study design for a non-inferiority, randomised controlled trial aimed to compare the short-term effect (the 3^rd^ to 8^th^ treatment week) of EA with prucalopride for severe chronic constipation. Acupuncture is a non-toxic, economical intervention with minimal adverse effects [16]. If the efficacy of EA is non-inferior to prucalopride, it may be a reasonable option for patients who do not want to experience the side effects of prucalopride. We also want to observe EA’s lasting effect, i.e., EA’s effect at the 3^rd^ and 6^th^ month post treatment. The EA group will be treated for 8 weeks and the prucalopride group will be treated for 32 weeks. A comparison between the two groups after the 8^th^ week could clarify the lasting and dominant effect of EA.

This trial was limited because the participants and acupuncturists could not be blinded. However, the outcome assessors and statistician will be blinded to the allocation.

In conclusion, the trial will compare the effect of EA to that of prucalopride for severe chronic constipation.

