## Background

Twelve percent of adults have constipation worldwide [1]. In China, the figure is 4%-6% [2, 3]. Severe chronic constipation is defined as two or fewer spontaneous, complete bowel movements (SCBMs) per week, hard stool and a sensation of straining during defecation [4]. Due to their widespread use, laxatives are an available choice for constipated patients. However, a high level of dissatisfaction has been reported for laxatives; specifically, evidence supporting the lasting effect of laxatives is limited [5–7]. A study of PEG3350 showed that 38.4 ± 14.1 days after the cessation of PG3350, 29 of 47 (61.7%) patients needed to take additional constipation treatment interventions [8]. A survey of 744 patients with chronic constipation in Europe showed that almost half were using alternative treatments (homeopathy, massage and acupuncture), and nearly 90% of respondents expressed interests in new therapies [6].

With a history of thousands of years, acupuncture has long been used to treat constipation in China. The systematic review [9] we have published concluded that acupuncture was safe for chronic functional constipation and might improve weekly spontaneous bowel movements (SBMs), the quality of life, and relevant symptoms. However, the evidence was limited by the small sample size and the methodological quality. A pilot study (n = 60) we have finished showed that 31.67% patients had 3 or more weekly SBMs after 8 weeks of treatment. By the third month, 40% patients still had 3 or more weekly SBMs, which reflected the lasting effect (effect post treatment) of acupuncture (to be published).

This report is a protocol of a phase-II trial aiming to evaluate the effect of electroacupuncture (EA) versus prucalopride for severe chronic constipation. The World Gastroenterology Organisation recommends prucalopride for patients for whom previous laxative use failed to provide satisfactory relief [10]. It was also considered effective and safe in a randomised controlled trial conducted in the Asia-Pacific region [11]. Thus, the use of prucalopride as the control drug in this trial is reasonable. The objective is to compare the effect of EA versus prucalopride for severe chronic constipation. We will also observe how many patients will not need additional medicine until the 3^rd^ and 6^th^ month post treatment. The safety and acceptance of EA will be simultaneously evaluated.

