**Table 1 Tab1:** **Secondary outcome measures**

No.	Outcome measure	Time frame	Statistics
1	Proportion of patients having ≥3 SCBMs/week	Week 1–2, week 9–12, week 9–16, week 9–20, week 9-32	CMH test
2	Proportion of patients with one or more increase in SCBMs/week from baseline	Week 1–2, week 3–8, week 9–12, week 9–16, week 9–20, week 9-32	CMH test
3	SCBMs/week and change from baseline	Week 1–2, week 3–8, week 9–12, week 9–16, week 9–20, week 9-32	Nonparametric test
4	SBMs/week and change from baseline in SCBM/week	Week 1–2, week 3–8, week 9–12, week 9–16, week9-20, week 9-32	Nonparametric test
5	Mean Bristol Stool Scale and change from baseline	Baseline, week 1–2, week 3-8	Nonparametric test
6	Straining degree	Week 1–2, week 3–8, week 9–12, week 9–16, week 9–20, week 9-32	Nonparametric test
7	Time to first SCBM	Time from the first treatment to the first SCBM	Nonparametric test
8	Patient assessment of Constipation Quality Of Life (PAC-QOL)	Baseline, week 1–4, week 5-8	*t* test or Mann–Whitney *U* test

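### The comparison after week 8 sets EA stopped against prucalopride continued, so by itself it does not isolate whether EA's effect lasts

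*Protocol article*

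**What the plan says.** The Discussion names durability as an aim: "We also want to observe EA’s lasting effect, i.e., EA’s effect at the 3" (the sentence goes on to the third and sixth months after treatment). It then gives the treatment durations, "The EA group will be treated for 8 weeks and the prucalopride group will be treated for 32 weeks", and concludes that a between-group comparison after week 8 "could clarify the lasting and dominant effect of EA".

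The Control group section makes the continuation conditional: after an ECG at week 8, "the drug will be taken for another 24 weeks in the absence of adverse events". No untreated, sham or drug-stopped arm is planned.

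Table 1, item 1, "Proportion of patients having ≥3 SCBMs/week", is analysed by CMH test over weeks 9–12, 9–16, 9–20 and 9–32, always for the whole arm. The section on sample size and statistical analysis makes every test two-sided except the primary, and ties the 10% margin to the weeks 3–8 outcome only. Diaries are kept "during the baseline assessment period, week 1–8, 11–12, 15–16, 19–20 and 31–32", which covers both the treatment weeks and about three and six months after EA ends.

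**The concern.** Whether EA's effect lasts is a question about EA patients after their treatment stops. The contrast named in the Discussion is EA withdrawn against drug continued, including control patients whose drug is stopped for adverse events. A given level of EA persistence can therefore look lost, equal or dominant according to how the drug arm fares. EA falling below prucalopride would not show that the effect had gone, because the comparator may still be on treatment. A non-significant two-sided test would not show that it had lasted.

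Whole-arm rates also do not distinguish early responders who hold from patients who first reach the threshold after treatment. The Background reads the pilot in this way: "By the third month, 40% patients still had 3 or more weekly SBMs, which reflected the lasting effect". At stake is what the trial may conclude on a named secondary aim.

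**Working it through.** **Inputs from the protocol article.** Expected weeks 3–8 rates: EA 31.6%, prucalopride 30.9%; placebo 12.0%; margin 10 points; one-sided 5%; power 80%; dropout 20%; 276 per group needed, 560 planned. Taking 1:1 allocation (inferred), 560/2 = 280 per arm, and 280 × 0.8 = 224 evaluable. All follow-up rates other than 31.6%, 30.9% and 12.0% are assumptions.

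**The plan's own figure.** It concerns the primary outcome only: n = (1.645 + 0.842)² × (0.309×0.691 + 0.316×0.684) / (0.10 + 0.007)² = 232.02, rounded up to 233. Multiplying by 1.2 gives 280, within 3% of the stated 276; dividing by 0.8 gives 292. No figure is stated for the comparison after week 8, so this does not bear on the point.

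**Step 1: one difference, several EA courses.** Difference d = pE − pP, with 95% CI d ± 1.96 × √[pE(1−pE)/224 + pP(1−pP)/224].

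| Scenario | EA | Prucalopride | Difference, points (95% CI) |
|---|---|---|---|
| Both hold | 31.6% | 30.9% | +0.7 (-7.9 to 9.3) |
| Both fall | 20.0% | 19.3% | +0.7 (-6.7 to 8.1) |
| Both near placebo | 12.7% | 12.0% | +0.7 (-5.4 to 6.8) |
| EA falls, drug holds | 20.0% | 30.9% | -10.9 (-18.9 to -2.9) |
| EA holds, drug rises | 31.6% | 42.5% | -10.9 (-19.8 to -2.0) |

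For the fourth row: √[(0.160 + 0.2135)/224] = 0.0408; 1.96 × 0.0408 = 0.080; -0.109 ± 0.080.

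**Step 2: what a two-sided 5% test can show.** Power = Φ[(|d| − 1.96·SE0)/SE1], with SE0 from the pooled rate and SE1 from the separate rates.

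| EA v prucalopride | 224 per arm | 280 per arm |
|---|---|---|
| 12% v 15% | 0.15 | 0.18 |
| 12% v 18% | 0.43 | 0.51 |
| 24% v 30.9% | 0.37 | 0.45 |
| 20% v 30.9% | 0.76 | 0.84 |
| 12% v 30.9% | >0.99 | >0.99 |

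If EA has dropped to the placebo rate and the drug arm has drifted to 18%, the test is non-significant 57% of the time (1 − 0.43); at 15% it is 85%. If the drug arm stays at 30.9%, EA must fall to about 19.4% (20.6% with 280 per arm) before power reaches 80%.

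**Step 3: the pilot.** 31.67% of 60 is 19 patients and 40% of 60 is 24. If the denominator is unchanged, at least 24 − 19 = 5 of the 24 were not responders at the end of treatment, so the later rate is not retention alone. These are SBMs, whereas Table 1, item 1 counts SCBMs. They illustrate the ambiguity of whole-arm rates and say nothing about how SCBM response behaves.

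**The case against.** A reader might infer that the contrast is worthless for durability. The documents do not support that. EA off treatment matching or beating a drug that still works would be evidence of persistence against a demanding comparator, and a fall to the placebo rate against a steady drug arm would almost certainly be detected. What remains is that the first argument needs the drug to be still working in follow-up, and without an untreated or drug-stopped arm the trial cannot verify this.

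A reader might also infer that nothing else bears on durability. In fact Table 1 gives each arm's responder rate and change in SCBMs from baseline through week 32, and the Background plans to observe how many patients need no additional medicine up to months three and six. The protocol's own meaning of lasting effect is the effect after treatment, which whole-arm rates do describe; sustained response is a different quantity and drops late responders.

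It is equally tempting to rest the claim on the EA arm alone. That would be uncontrolled: patients enter at a low bowel-movement count, so regression to the mean and natural course would be credited to EA. Requiring response in weeks 3–8 first does not remove this.

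Finally, the scenarios with prucalopride at 15% or 18% assume that the continued drug loses most of its advantage over placebo, which no figure in the document supports. The sentence at issue is also hedged, and the unequal durations are stated openly. These objections limit the point but do not rescue the inference: a single between-arm result still fits both a kept and a lost EA effect.

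**Conclusion.** The point holds in a limited form. The contrast after week 8 compares two treatment strategies and does not by itself identify persistence of EA. In the scenarios above, +0.7 points fits full retention or a return to about the placebo rate, and -10.9 points fits either loss or full retention. A moderate loss (24% against 30.9%) would be missed about 63% of the time at 224 per arm and 55% at 280, so the conclusion does not hang on the dropout assumption. It does rest on assumed follow-up rates and inferred 1:1 allocation. The effect is confined to a secondary aim; the weeks 3–8 comparison, its margin and its sample size are untouched.

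**What to change.** 1. In the Discussion, replace the claim that the comparison clarifies EA's lasting and dominant effect. State instead that the week 9–32 contrast compares two strategies: 8 weeks of EA then none, against prucalopride continued. Report it as a difference in proportions with a 95% CI, and say that a non-significant test will not be read as a lasting effect.
2. Add a supplementary item to Table 1: per arm, with 95% CI, the proportion of all randomised patients who respond in weeks 3–8 and still have at least 3 SCBMs per week in the post-treatment diary periods. Show it beside the whole-arm rates already planned.
3. Describe EA's durability from both together, labelled descriptive. State that natural course and regression to the mean cannot be separated from carry-over of EA.

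This costs wording and one extra tabulation from diaries already scheduled, with no new data. The price is a more modest claim about lasting effect.
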